### Implementation and evaluation of practice changes to improve outcomes

Practices identified as being associated with an improvement in outcomes will be proposed to network sites for implementation using the continuous cycle of application and evaluation central to the EPIQ method [34,35]. Quality improvement using EPIQ methodology has been implemented in Canadian NICUs for the last 10 years. It is based on three pillars: (1) the use of all available evidence on a particular intervention from the published scientific literature, (2) analysis of each institute’s baseline data to identify hospital-specific practices for targeted intervention, and (3) the use of a network to share the results of quality improvement for the purpose of collaborative learning. The EPIQ method utilizes local context and allows customization of interventions and implementation strategies to maximize improvement potential at each institute. This is conducted in conjunction with leadership and peer support from network members [34,35].

Our plan for the iNeo network is to expand the EPIQ approach to an international level. We will advocate incorporation of several cycles of practice change implementation, evaluation, monitoring, and collaborative learning within each unit over the course of two and a half years. The online ViviWeb Virtual Research Community (https://meta.cche.net/viviweb/default.asp) will be used to facilitate collaboration between networks. Based on our experiences and preliminary results implementing practice changes in Canada, and following discussion with the NRNJ, we anticipate that regular and productive dialogue will significantly benefit many of the participating NICUs.

The practice changes implemented by individual units within networks will be evaluated every 6 to 12 months depending upon each centre’s capabilities to collect and submit data. In addition to outcome indicators, process indicators will be developed based on the specific interventions implemented. These indicators will measure the short-term impact of practice change. For example, an intervention targeting early surfactant administration to reduce BPD will have process indicators for the time of first surfactant administration and the proportion of babies who received surfactant within the first 30 minutes after birth. The outcome of interest for this intervention will be reduction in the incidence of BPD. Safety and outcome improvements will be monitored within each unit and network using control charts and Chi-square tests for differences in outcome rates from baseline. Multivariable logistic regression analyses will pool data from units within each network to assess changes in outcomes over time with adjustment for potential confounders and important risk factors, and accounting for clustering.

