## Methods/design

### Overview

The comparison of neonatal mortality and morbidity between the eight member networks will be conducted using four years of retrospective data collected between January, 2007 and December, 2010. Subsequently, a strategy will be designed to collect additional data and assess differences in physical, environmental, and human characteristics, and care practices associated with variations in outcomes between networks. Once identified, clinical and organizational practice improvements will be implemented within networks using the Evidence-based Practice for Quality Improvement (EPIQ) method [34,35]. The effect of practice change implementation will be measured using ongoing data collection within each network. The total study period will be five years (January 2013 to December 2017). Comparison between the networks will be completed by early 2014, associations between external factors/care practices and outcomes identified by the end of 2014, and selected practice changes implemented by mid 2015. This will be followed by a two and a half-year period of continuous quality improvement within the networks.

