### Participating networks

The following neonatal networks have agreed to participate in the iNeo project: Australia-New Zealand Neonatal Network (ANZNN), Canadian Neonatal Network (CNN), Israeli Neonatal Network (INN), Neonatal Research Network of Japan (NRNJ), Spanish Neonatal Network (SEN1500), Swedish Neonatal Quality Register (SNQ), Swiss Neonatal Network (SNN), and UK Neonatal Collaborative (UKNC) (see Table 1). Overall, this project will be collecting data from a total of 251 NICUs in nine countries caring for approximately 23,000 to 24,000 VLBW neonates per year. All the participating networks have a common mandate to collect, analyze, and benchmark performance and outcomes of their respective NICUs. We have carefully avoided networks that only include highly specialized units in order to obtain robust population-based estimates. All participating networks have confirmed the feasibility of data collection from >75% of all VLBW and VPT infants born within their country. The approximately 25% of infants missing from some of the networks are those considered to be at the higher end of maturity (>1300 g birth weight or >30 weeks gestation) who do not require intensive care support. These infants are relatively stable and do not represent a significant burden to NICUs or health care services in general.

**Table 1 T1:** Characteristics of networks participating in the International Network for Evaluating Outcomes of Neonates (iNeo)

**Network**	**Australia and New Zealand Neonatal Network**	**Canadian Neonatal Network**	**Israeli Neonatal Network**	**Neonatal Research Network Japan**	**Spanish Neonatal Network**	**Swedish Neonatal Quality Register**	**Swiss Neonatal Network & Follow-****Up Group**	**UK Neonatal Collaborative**
Country	Australia and New Zealand	Canada	Israel	Japan	Spain	Sweden	Switzerland	UK (England)
Level III NICUs in the country	23 + 6	30	23	93	n/a	7	9	45
Level III NICUs in the network	29	30	23	73	36	7	9	44
Number of inhabitants	Australia: 23 million NZ: 4.4 million	34 million	7.9 million	126 million	47 million	9.5 million	8 million	52 million
Number of births/year	Australia: 300,000 NZ: 60,000	380,863	166,000	1,071,304	497,023	110,000	80,000	687,000
Number of eligible NICU admissions/year (<32 wks gestation/<1500 g)	3,500	2,700	1,500	3,700	2,600	900	800	7,700

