#### Statistical analyses and power for identification of practice and service variation

Associations of clinical management practices and other external factors with outcomes will be assessed under the general framework of individual patient-level data meta-analyses. Random-effects models with adjustment for confounding variables and important risk factors will provide estimates of association and quantify residual variation due to unknown or unmeasured unit-specific and network-level factors. These analyses will identify treatment practices and health care services with significant impact on outcomes, which subsequently can be targeted for implementation or improvement by specific units or networks. This information along with details of the practices/factors will be made available to initiate discussion within the iNeo community regarding data-informed, evidence-linked potentially better practices. Analyses (two-sided tests) based on 10,000 yearly admissions evaluating impact of treatment/practices (assuming 50% exposure) on outcomes (incidence 1% to 40%) will be able to detect relative risks of 1.6 to 1.1 with statistical power of 80% and 5% type I error rate. This is a conservative power calculation based on data expected to be collected in a one-year timeframe.

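### Unit-level Chi-square tests every 6 to 12 months rest on about 47 to 93 infants in an average unit: for uncommon outcomes they can hardly show improvement, and false flags lean to harm when the baseline is longer than the window

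*Protocol article*

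**What the plan says.** In the section on implementing and evaluating practice changes, the protocol article states that changes made by individual units "will be evaluated every 6 to 12 months", depending on each centre's capacity to submit data. Safety and outcome improvement are then "monitored within each unit and network using control charts and Chi-square tests for differences in outcome rates from baseline". The same paragraph adds process indicators and a network-level analysis: "Multivariable logistic regression analyses will pool data from units within each network to assess changes in outcomes over time", adjusted for confounders and clustering. The quality improvement period lasts two and a half years.

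Under Participating networks, the project covers "a total of 251 NICUs in nine countries caring for approximately 23,000 to 24,000 VLBW neonates per year". The power statement on practice variation is set for 10,000 yearly admissions and says that analyses of "outcomes (incidence 1% to 40%) will be able to detect relative risks of 1.6 to 1.1", at 80% power and a two-sided 5% level. The other power statement covers comparisons between networks. Neither covers a single unit.

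**The concern.** The test, the level at which it is applied and its frequency are all stated, so this is a choice made in the document and not a detail left open. A Pearson Chi-square test is a large-sample test. With 47 infants the expected number of events in the window is below 5 for any outcome under 5/47 = 10.6%, while the plan works with outcome rates down to 1%. If the baseline is several times larger than the window, the test statistic is skewed as well: few events can be lost from an already small count, but a few extra events are enough to cross the upper limit.

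A unit that truly halves an uncommon morbidity would then rarely see a significant result, and a unit with no change would be flagged for harm more often than for benefit. This matters because the improvement method is tailored to each institution, and a pooled network result does not tell a unit whether its own change worked.

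**Working it through.** **The plan's own figure first.** Take 5,000 exposed and 5,000 unexposed (50% of 10,000), two-sided 5% and 80% power. Solving n = [1.96·√(2·p̄·(1−p̄)) + 0.84·√(p₁(1−p₁)+p₂(1−p₂))]² / (p₁−p₂)² for n = 5,000 gives a relative risk of 1.64 at 1% and 1.07 at 40%. That matches the stated 1.6 to 1.1, so the power statement is sound for its own purpose. It says nothing about a unit of 47 to 93 infants.

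**Unit size.** The Table 1 admissions sum to 3,500 + 2,700 + 1,500 + 3,700 + 2,600 + 900 + 800 + 7,700 = 23,400 per year in 251 network units. 23,400/251 = 93.2 per unit-year, or 46.6 per 6 months. Network averages differ: Japan 3,700/73 = 51 per year (25 per 6 months), UK 7,700/44 = 175 per year.

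**Assumptions, because the article does not fix them.** Baseline: the retrospective period, "four years of retrospective data collected between January, 2007 and December, 2010", so 4 × 93.2 = 373 infants, with shorter baselines as the range. Test: Pearson, two-sided 5%, each window tested alone.

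**Zero events in the window.** With window n, baseline m, N = n + m and b baseline events, zero window events give X² = N·n·b / [m·(N−b)], to be compared with 3.84.

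- n = 47: b = 28 gives 3.78 and b = 29 gives 3.93. The limit is 29/373 = 7.8%.
- n = 93: b = 14 gives 3.60 and b = 15 gives 3.86. The limit is 15/373 = 4.0%.

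Fisher's exact test gives 8.0% and 4.0%. The continuity-corrected test gives 9.9% and 5.4%. For baselines between 47 and 373 infants, the 6-month Pearson limit stays between 7.8% and 8.6%.

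**Power for a true halving in one window (exact enumeration, baseline 373).**

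| Baseline rate | 6 months | 12 months |
|---|---|---|
| 5% | 0.4% | 12% |
| 10% | 13% | 30% |
| 20% | 37% | 64% |
| 40% | 80% | 97% |

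**Any flag over the two and a half years (simulation, 400,000 runs, 5% rate).**

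| Baseline, windows | False harm | False improvement | True halving flagged as improvement |
|---|---|---|---|
| 373, five of 6 months | 16.2% | 0.5% | 1.1% |
| 186, five of 6 months | 13.9% | 1.8% | 4.0% |
| 93, five of 6 months | 10.6% | 3.7% | 7.9% |
| 47, five of 6 months | 9.5% | 9.2% | 17.8% |
| 373, two of 12 months | 6.3% | 3.0% | 21.7% |
| 93, two of 12 months | 3.6% | 4.0% | 20.5% |

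The imbalance also fades as outcomes become more common. For one 6-month window with baseline 373, the ratio of false harm to false improvement is about 31:1 at 5%, 2.8:1 at 8% and 1.1:1 at 40%.

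**Accumulated alternative.** One test at the end on all infants since the change, baseline 373, halving from 5%:

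- Five 6-month windows (235 infants): Pearson detects 31% and mid-P 34%, against 1.1% window by window. With no change, mid-P errs about 2.4% in each direction. Most of the power gain therefore comes from accumulating.
- Two 12-month windows (186 infants): mid-P detects 27%, against 22%.
- Two 12-month windows with a one-year baseline: mid-P detects 20%, against 21%, so there is no gain.

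These are single final tests. Controlling the error over repeated looks would lower them somewhat.

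**Control chart.** The article does not name a type. If it were a standard 3-sigma p-chart, the lower limit p − 3√(p(1−p)/n) is at or below zero when p ≤ 9/(n+9): 16% for n = 47 and 9% for n = 93. It would have the same blind spot.

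**The case against.** A reader might infer that each unit is judged by the Chi-square test alone, that no improvement can be shown for any outcome under 8%, and that false harm flags outnumber false improvement flags by 30 to 1 or more. The documents do not support this. The 8% limit belongs to the 6-month end of the stated interval; at 12 months it is about 4%. A ratio of about 30:1 needs a rate near 5%, 6-month windows and a four-year baseline together. It is about 2:1 at 12 months, about 3:1 with a one-year baseline and 1:1 with an equal-sized one.

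Other points also stand. Testing each window alone is a reading: the wording would also fit a cumulative look at each evaluation. Control charts are named beside the test, and a CUSUM is a control chart. Chart type, small-count rules and accumulation are details that an article may leave to a fuller plan. Process indicators, network-level tests and the pooled, adjusted, clustered regression give further evidence, and no passage makes the unit-level test a decision rule. With 12-month windows the main limit is unit size, which no change of analysis removes.

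What remains is that the article does choose a large-sample test against baseline at unit level, repeated every 6 to 12 months, in units this small. The network analyses are large enough, but they answer a different question from whether a given unit's own change worked.

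**Conclusion.** The point holds as a recommendation on unit-level monitoring, not as a defect of the programme's main comparisons. For an average unit, and under the assumed four-year baseline with separate windows, improvement in outcomes below about 8% (6 months) or about 4% (12 months) cannot reach significance even with no events. Over five 6-month windows, a halving from 5% is flagged in about 1% of units, while an unchanged unit is flagged for harm in about 16% and for improvement in 0.5%. The low power for uncommon outcomes holds across the baselines examined. The lean to harm depends on the baseline being longer than the window, which the article does not settle. Units smaller than average, such as the typical Japanese unit, fare worse; larger ones, such as the typical UK unit, fare better.

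**What to change.** At unit level, replace the Chi-square test by an exact mid-P test on all infants accumulated since the change. State the baseline period and the false-alarm rate across the repeated looks. For uncommon outcomes, specify the control chart as a CUSUM or time-between-events chart with separate upper and lower limits. Keep Chi-square tests for network level, where the counts are large enough.

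The cost is wording and some chart programming, with no new data. There are two drawbacks: an accumulated test reacts more slowly to a recent reversal, and it adds little or no power where windows are 12 months.

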### Association of site characteristics and practices with outcomes

To identify factors contributing to outcome variation between networks, detailed information will be obtained on health service provision, including units’ physical layout, environmental characteristics, human factors, and management practices at the national and site level. The type of data and strategy for collecting this information will be determined following the comparison of outcomes between networks to target identified problem areas and evaluate the culture, context, and practices of each network. Factors with possible impact on outcome differences between and within networks will be ascertained using a variety of tools, such as surveys, recurring questionnaires, and in specific instances, site visits to explore details if permitted.

The data will be pooled across sites and networks, and statistical analyses will identify factors significantly associated with outcomes. Through a collaborative process, findings will be discussed with members of participating networks to select physical and environmental factors, human and resource factors, or processes of care that can be modified through a quality improvement process. Each network will then implement practice changes within these three main target areas according to their outcome priorities and the constraints of their respective health care systems.

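### The practice-change evaluation is a within-network before-after contrast with no defined baseline, modelled prior trend or concurrent comparison, so it cannot isolate the programme's effect

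*Protocol article*

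**What the plan says.** Aim 4 under Network objectives is to implement practice changes and keep evaluating their impact. The section Implementation and evaluation of practice changes to improve outcomes says changes will be "evaluated every 6 to 12 months" over two and a half years. Safety and improvement are tracked, for single units and for whole networks, "using control charts and Chi-square tests for differences in outcome rates from baseline". The next sentence adds a second analysis: "Multivariable logistic regression analyses will pool data from units within each network to assess changes in outcomes over time". The article specifies that this model is to be run "with adjustment for potential confounders and important risk factors, and accounting for clustering".

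The Overview says the effect will be measured from continuing data collection inside each network. The only outcome data set it dates is "four years of retrospective data collected between January, 2007 and December, 2010", which it assigns to the between-network comparison. Practice changes are due by mid 2015. The evaluation section does not say which period is baseline.

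Targets depend partly on observed results. Care-provision factors sorts networks by performance on each secondary outcome. Association of site characteristics and practices with outcomes says "Each network will then implement practice changes within these three main target areas according to their outcome priorities", subject also to health-system constraints. One pillar of the quality-improvement method is to examine every hospital's own "baseline data to identify hospital-specific practices for targeted intervention".

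**The concern.** Every analysis named for this phase compares a unit or network with its own past. Two things other than the programme can produce such a difference.

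- **Secular trend.** The Background reports long improvement followed, in some networks including the Canadian one, by a stall or worsening. Outcomes therefore move without this programme.
- **Regression to the mean.** Where a target is picked because its observed rate was high, and the follow-up rate is compared with those same data, part of the excess disappears by chance.

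Adjusting for case mix and clustering removes neither. At stake is the answer to Aim 4: a fall already under way could be read as benefit, a worsening trend could hide benefit, and repeated testing could raise false alarms on safety.

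**Working it through.** The plan gives no sample size, significance level or effect size for this phase, so there is no stated figure to reproduce. The checks below assume a two-sided 5% level, as in the article's power statements. Event rates, drift and intraclass correlation (ICC) are also assumptions.

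**Inputs from the article.** There are 251 NICUs. The yearly admissions in Table 1 sum to 23,400, so an average unit has 23,400 / 251 ≈ 93 a year, or about 373 in four years. Canada has 2,700 a year and 10,800 in four years. Reviews every 6 to 12 months over 2.5 years give about two to five looks.

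**1. Secular trend, baseline 2007-2010, no programme effect.** Compare 10,800 with 2,700 infants, assumed rate 30%.
- Fall of 2 points: pooled rate 0.296; SE = √[0.296 × 0.704 × (1/10,800 + 1/2,700)] = 0.0098; z = 0.02 / 0.0098 ≈ 2.04. Probability of significance ≈ 53%.
- Fall of 3 points: z ≈ 3.06. Probability ≈ 87%.

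A second set assumes a 25% rate and a relative decline of 1, 2 or 3% a year over 7 years (end of 2008, the baseline midpoint, to the middle of the first post-change year). The follow-up rate is 25% × 0.99⁷, 0.98⁷ or 0.97⁷ = 23.3%, 21.7% or 20.2%. Probability of a significant fall:

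| Comparison | 1%/yr | 2%/yr | 3%/yr |
|---|---|---|---|
| Canada, baseline 2007-2010 | 0.45 | 0.95 | >0.99 |
| Average unit, baseline 2007-2010 | 0.05 | 0.09 | 0.15 |
| Canada, baseline = year before change | 0.04 | 0.06 | 0.09 |

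The nominal rate in that one direction is 2.5%.

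**2. Regression to the mean.** Reliability = n × ICC / (n × ICC + 1); expected fall = 10 points × (1 − reliability) for a unit observed 10 points above average.
- One-year baseline, n = 93: ICC 0.01 gives 0.93 / 1.93 = 0.48, a fall of 5.2 points; ICC 0.02 gives 1.86 / 2.86 = 0.65, a fall of 3.5.
- Four-year baseline, n = 373: 3.73 / 4.73 = 0.79, a fall of 2.1; 7.46 / 8.46 = 0.88, a fall of 1.2.
- Network, n = 10,800, ICC 0.01: 108 / 109 = 0.99, a fall of about 0.1 point, which is negligible.

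As a cross-check, a simulation took the worst quarter of 251 units with no true change (25% rate, between-unit SD 0 to 0.4 on the logit scale). False improvement per look was 3 to 9%, against a nominal 2.5%.

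**3. Repeated looks, no true change.** Independent looks give 1 − 0.95² = 9.8% and 1 − 0.95⁵ = 22.6%. Simulation with one shared baseline, one to eight times the size of each look, gives 9.1 to 9.8% for two looks and 18 to 22% for five, per unit and outcome. At 22%, that is 0.22 × 251 ≈ 55 units; at 9 to 10%, about 23 to 25.

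**The case against.** A reader might infer that impact is judged by unadjusted chi-square tests alone. The text does not support that: those tests are described as monitoring, beside control charts, and an adjusted, clustered regression follows. Process indicators are also planned and would help attribution.

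Nor does the article say that baseline is 2007-2010. Ongoing network data make a recent local baseline at least as plausible, and the drift problem is then much smaller. The worst cases also cannot be added together, because a long, old baseline enlarges drift and shrinks regression to the mean, while a short, recent one does the reverse.

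It would also be too strong to say that trend will be credited to the programme. The Background's report of worsening in some networks would bias against it. Selection on poor results is only partial, since published evidence and system constraints also shape targets. Five looks is the upper limit.

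Finally, an article may leave the form of the time term to a fuller document, and it could turn out to be segmented. That stands as far as the time term goes. It does not reach the design the article does state: measurement within each network, differences from baseline, pooling by network. Those choices leave out a concurrent comparison whatever the time term.

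**Conclusion.** The point holds in limited form. The evaluation as stated is an uncontrolled before-after comparison with an undefined baseline and partly outcome-driven targets. Case-mix adjustment and clustering do not separate the programme from calendar time or from regression to the mean, and the bias can run either way.

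The size is conditional on the assumed rates, drift and ICC. Drift is serious at network level if baseline is 2007-2010 and modest if baseline is the preceding year. Regression to the mean matters for single units, mainly with a one-year baseline. False signals from repeated looks range from about 9% to 22% per unit and outcome. No choice of baseline window removes all of these. This limits causal claims under Aim 4; it does not make the monitoring worthless.

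**What to change.** - Define the baseline period. Keep control charts for local monitoring, and state that the chi-square tests will not be used to claim impact.
- Make the effect analysis a segmented mixed logistic model with a calendar-time trend, case-mix terms, a NICU random intercept, and a step and slope at each unit's implementation date.
- Use all available quarters before implementation, including 2011 to 2015.
- Include units or networks not targeting that outcome, in the same quarters, as a contemporaneous comparison.
- Record which data were used to choose each target, so that a sensitivity analysis can leave them out. The comparison units deal with shared trend but do not by themselves remove regression to the mean in units selected for high rates.

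The cost is analysis wording, programming, and extraction of the intervening records from ongoing network data collection. The contrast may be diluted because results are shared across the network by design, and because the same quality-improvement method has already run in Canadian NICUs for ten years. The report should say so.
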